## Discussion

This is the first study conducted to investigate the effect of the recognition of depression and anxiety and the subsequently initiated treatment by the GP on the quality of life and the prognosis of heart failure in HF patients in primary care. The results are expected to glean important insights into the care for HF patients in primary care.

### Expected implications for practice

We will be able to show how many heart failure patients in primary care suffer from depression and anxiety. We will display the frequency of GP-acknowledged depression/anxiety and the factors which may facilitate and exacerbate the recognition. Based on these results, patient characteristics which exacerbate recognition will be reported to GPs. Such knowledge will assist the GP in judging which HF patient may benefit from additional attention paid to symptoms of depression and anxiety. The frequency of installed therapeutic strategies and the impact of the different therapeutic approaches on quality of life and heart failure prognosis found in this study will be displayed. These results will be provided to GPs and will give a first orientation of which therapeutic strategies might be helpful for HF patients, not only to reduce depression, but also to improve their quality of life and prognosis of heart failure.

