## Methods/Design

The study is designed as a multicenter, prospective, observational study investigating 3,950 primary care patients with HF in Germany. The following research questions will be addressed:

● How many patients with HF suffer from depression and/or anxiety?

● How are the recognition rates of depression and/or anxiety by general practitioners (GPs)?

● How often are which measures taken by the GP when depression and/or anxiety are recognized?

● Is there an association between the presence of depression and/or anxiety and quality of life and HF prognosis (hospital admittance and mortality risk)?

● Is there an association between the recognition of present depression/anxiety by the GP and quality of life and HF prognosis (mortality, hospital admissions)?

● Which factors are associated with non-recognition and with failure to initiate adequate interventions (pharmacological or psychotherapeutical)?

● Is there an association between the presence and the recognition of depression/anxiety by the GP and health care aspects (e.g. frequency of contacts with the GP)?

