**Inclusion Criteria**			
Informed consent	✓	✓	✓
Aged 18 years and older	✓	✓	✓
Diagnosis of heart failure within the last 5 years, validated by the GP on basis of his medical records	✓	✓	✓
At least one contact with the participating GP within the last 6 month	✓	✓	✓
Depression and/or anxiety	✓	✓	
Recognition of existing depression and/or anxiety by the GP	✓		

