**Figure 1 F1:**
[figure not shown]
Baseline and follow-up assessment.

The 75% randomly selected patients without depression and/or anxiety provides a higher number of patients in the observation group 3 (P−/−) than the power calculation suggests (see section *Sample size calculation*). The higher number is chosen for quality assurance. A group of patients without depression and anxiety which is too small would reveal the focus on depression and anxiety in this study. Therefore the proportion of patients with depression and/or anxiety and without depression/anxiety will be 1:3 in each interview.

Symptoms of anxiety and depression are addressed within a full list of somatic comorbidities, introduced by the somatic conditions of the Charlson Comorbidity Index [46] and followed by a question concerning any further comorbidity, which has not been addressed in the list before. The focus on depression and anxiety within this study is not revealed to the GPs. During the interview the GPs have full access to all patient data within their electronic records. The recognition of depression and/or anxiety is operationalized as the GP’s judgement in the telephone interview as to whether or not the patient displays symptoms of depression and/or anxiety. If the GP states that the patient displays symptoms, the GP is asked if he or she judges this as a clinical diagnosis or if he or she considers the symptoms not severe enough for a diagnosis.

In a next step, patient information from the questionnaire and GP judgment regarding depression and anxiety are matched and the patients are allocated to one of the following groups:

● Observation group 1 (P +/+): All patients with depression and/or anxiety whose depression and/or anxiety has been recognized by the GP

● Observation group 2 (P +/−): All patients with depression and/or anxiety whose depression and/or anxiety has not been recognized by the GP

● Observation group 3: P (−/−) Sample of patients without depression and anxiety who were randomly selected for telephone interview. In the interview the GPs did not diagnosed any depression or anxiety.

Patients without depression and anxiety whose GP nevertheless diagnosed depression or anxiety P(−/+) will be considered separately.

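### Factors of non-recognition, defined only among affected patients, are to help GPs choose which heart failure patients merit extra attention; that use needs the risk of a missed case among patients the GP has not labelled

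*Protocol article*

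**What the plan says.** Only the protocol article is at hand. Four places in it bear on this point.

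- **Research questions (Methods/Design).** One question reads: "Which factors are associated with non-recognition and with failure to initiate adequate interventions".
- **Group definitions.** In the Methods section on recognition of depression and anxiety, observation group 2 (P+/−) is "All patients with depression and/or anxiety whose depression and/or anxiety has not been recognized by the GP". Table 1 gives group 1 (P+/+) the criterion "Recognition of existing depression and/or anxiety by the GP". Being recognized or not is thus defined only for patients who have depression and/or anxiety. Group 3 (P−/−) is a random 75% per practice of the patients without either condition; of these it is said that "In the interview the GPs did not diagnosed any depression or anxiety". Unaffected patients whom the GP nevertheless labels (P−/+) are set aside for separate consideration.
- **Data analysis.** The first step compares outcomes between affected patients and P−/−. The second compares outcomes between P+/+ and P+/−. The third concerns treatments. No step contrasts P+/− with P−/− by patient characteristics.
- **Expected implications for practice (Discussion).** The article states that "patient characteristics which exacerbate recognition will be reported to GPs", where the context shows that making recognition harder is meant. It continues: "Such knowledge will assist the GP in judging which HF patient may benefit from additional attention paid to symptoms of depression and anxiety".

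**The concern.** The last step changes the population. The research question concerns affected patients: given depression or anxiety, which of them does the GP miss? The use announced for the answer concerns heart failure patients in general: to whom should the GP pay more attention?

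The GP cannot condition on being affected, because that is what is unknown. Extra attention can find a missed case only among unlabelled patients, that is P+/− plus P−/−. How often a characteristic occurs among missed cases there depends both on how hard it makes recognition and on how common depression or anxiety is among its carriers. Factors of non-recognition carry only the first part.

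At stake is the practical message to GPs. A characteristic could be reported as a reason for extra attention although its carriers hold no more missed cases than other unlabelled patients, or fewer.

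**Working it through.** **Inputs from the article (Sample size calculation).** Prevalence of depression and/or anxiety 20%; recognition rate 75%, so 25% are missed; 10,973 invited; participation 40%; return of the baseline questionnaire 90%. The sampling fraction of unaffected patients, 75%, is in the Methods section on recognition.

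**The plan's own figures reproduce.**
- 10,973 × 0.40 × 0.90 = 3,950 at baseline.
- 3,950 × 0.20 = 790 affected; 790 × 0.25 = 197.5, about 198 missed.
- (3,950 − 790) × 0.75 = 3,160 × 0.75 = 2,370, as stated.

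**Two different quantities.** Let p be the prevalence, m the probability of being missed if affected, and s the probability that an unaffected patient is not labelled.
- Non-recognition among the affected: m = 25%.
- Missed cases among the unlabelled: p·m / [p·m + (1 − p)·s].

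The product p·m = 0.20 × 0.25 = 5.0% is the share of all patients. Among unlabelled patients, with P−/+ ignored (s = 1), the share is 0.05/(0.05 + 0.80) = 0.05/0.85 = 5.9%, or in counts 197.5/(197.5 + 3,160) = 197.5/3,357.5. The article gives no rate for P−/+. If GPs label 5% to 20% of unaffected patients, the share is 0.05/(0.05 + 0.76) = 6.2% to 0.05/(0.05 + 0.64) = 7.2%.

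**How a characteristic X acts.** Write 1 for carriers and 0 for non-carriers. With s = 1, the odds of being a missed case among unlabelled patients are p·m/(1 − p), so

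OR among unlabelled = [p1/(1 − p1)] / [p0/(1 − p0)] × (m1/m0) = prevalence OR × non-recognition risk ratio.

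A flagged characteristic (m1 > m0) reverses only if its prevalence OR falls below m0/m1.

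**Illustrations.** These are assumptions. X is carried by half of the patients, and the margins are held at 20% prevalence and 25% missed, so p0 = 0.40 − p1 and m0 = (0.25 × 0.40 − p1·m1)/p0. In the first row, m0 = (0.10 − 0.12 × 0.35)/0.28 = 0.058/0.28 = 20.7%.

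| Prevalence, X v not X | Missed, X v not X | OR for non-recognition | Prevalence OR × risk ratio | OR among unlabelled | Missed-case share, X v not X |
|---|---|---|---|---|---|
| 12% v 28% | 35% v 20.7% | 2.06 | 0.351 × 1.690 | 0.59 | 4.6% v 7.5% |
| 15% v 25% | 35% v 19% | 2.30 | 0.529 × 1.842 | 0.98 | 5.8% v 6.0% |
| 20% v 20% | 35% v 15% | 3.05 | 1 × 2.33 | 2.33 | 8.0% v 3.6% |
| 10% v 30% | 40% v 20% | 2.67 | 0.259 × 2.00 | 0.52 | 4.3% v 7.9% |
| 15% v 25% | 40% v 16% | 3.50 | 0.529 × 2.50 | 1.32 | 6.6% v 5.1% |

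First row in full: OR for non-recognition (0.35/0.65)/(0.207/0.793) = 2.06; shares 0.042/(0.042 + 0.88) = 4.6% and 0.058/(0.058 + 0.72) = 7.5%; OR among unlabelled (0.042/0.88)/(0.058/0.72) = 0.59.

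**Sampling weight.** Without weighting, the study data would show 197.5/(197.5 + 2,370) = 7.7% in place of 5.9%. Weighting P−/− by 1/0.75 restores 2,370/0.75 = 3,160. Because the fraction is the same in every practice, odds ratios hardly change.

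**The case against.** The strongest reply is that no analysis is wrong. Comparing P+/− with P+/+ is the correct answer to the research question. The sentence at issue is a soft statement of expected implications. It promises neither a risk ranking nor a screening rule, and it can be read as telling GPs in which patients symptoms are hard to see, to be combined with their own judgement. The article spells out no model for this question, and a plan not shown may contain more.

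Much of this stands. The recognition analysis is sound, and that it is restricted to affected patients follows from the group definitions, not from a written model. But the article itself draws the step from recognition factors to which patients may benefit, and a better-specified P+/− v P+/+ model would not supply what that step needs. Nor does the promised overall frequency of depression and anxiety, because prevalence by characteristic is the missing part.

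Two stronger readings are tempting. A reader might infer that the study will send GPs to the wrong patients. The article does not support that: it gives only the 20% and 75% margins, nothing in it shows that a hard-to-recognize characteristic goes with much lower prevalence, and two of the five illustrations show no reversal. A reader might also infer that P+/− is never compared with P−/−. That is too broad: the study endpoints section names all three groups for comparison, and the sample size section considers EQ-VAS differences between them. What is absent is a contrast by patient characteristics.

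**Conclusion.** The point holds in a limited form. The announced use needs the probability of depression or anxiety among unlabelled patients (5.9% at the planning figures, 6.2% to 7.2% if 5% to 20% of unaffected patients are falsely labelled), while the factors to be reported describe non-recognition among the affected (25%). The two can rank a characteristic differently. How far depends on how prevalence varies with it: they agree in direction when prevalence is equal or only mildly lower among carriers, roughly cancel in the 15% v 25% example with 35% missed, and reverse when prevalence is clearly lower.

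The size of any reversal rests on assumed stratum figures and on ignoring P−/+; false labelling that differs by characteristic would change the odds ratio further. Recruitment, group allocation, the primary outcome and the planned outcome comparisons are unaffected. The matter is confined to what the study may tell GPs, where it is worth correcting.

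**What to change.** Keep the P+/− v P+/+ analysis to explain why cases are missed. For the message to GPs, do one of the following.

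1. Add a logistic model at baseline of P+/− v P−/− among patients whose GP reports no depression or anxiety, using predictors that the GP can see. Report the absolute missed-case share for each characteristic, with P−/− weighted by 1/0.75, next to the odds ratios.
2. Otherwise, limit the sentence under Expected implications for practice to saying in which affected patients recognition fails, without extending it to which heart failure patients may benefit from attention.

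The first option needs no new data: baseline questionnaires and GP interviews exist for both groups, and follow-up is not required. Its cost is one more secondary model with about 198 events, which limits the number of predictors and should be labelled exploratory. The second option costs one reworded sentence.

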### Expected implications for health policy

Public health planners are in need of numbers such as frequency of depression and anxiety as well as frequency of different treatment options substantiating the decision process of resource allocation. For the health planners we will describe the frequency of depression and/or anxiety missed by GPs and the potential treatment gap.

Such a treatment gap with respect to psychosocial problems in HF patients is currently unproven but needs to be assumed if preliminary findings are transferred onto the general population. If so, more resources should be spent on investigating effective treatments.

For these investigations the differential effects of correctly acknowledged and missed depression and/or anxiety on outcome, also in comparison to the outcome of subjects without depression and/or anxiety, will help to better understand how health care for HF patients needs to be improved and which treatment might be effective. We will be able to present evidence to what extent the recognition of depression and/or anxiety through screening for depression and anxiety is mandatory for HF patients, as already recommended in clinical guidelines.

### Expected implications for research

The results of this study will help to generate hypotheses regarding effective treatment of depression and anxiety and the potential effects on the quality of life and prognosis in patients with HF. In a next step these hypotheses can be tested by intervention studies. The case-finding algorithm to identify HF patients with depression and anxiety obtained from the sub-study could be recommended for further observational and intervention studies in HF patients and is likely to reduce the huge variation of reported prevalence rates. In addition, this study will provide methodological support for efficient planning of further interventional research.

## Abbreviations

EQ-VAS: EQ-5D visual analogue scale; GP: general practitioner; GAD 7: Patient health questionnaire 7-item subscale generalised anxiety disorder assessment; HF: Heart failure; HADS: Hospital anxiety and depression scale; HASD-D: Hospital anxiety and depression scale – subscale Depression; HASD-A: Hospital anxiety and depression scale – subscale Anxiety; PHQ-9: Patient health questionnaire – 9 item depression subscale; PROMIS: Patient-reported outcomes measurement information system; SCID: Structured clinical interview for DSM-IV.
